# Improving patient-centeredness of fertility care using a multifaceted approach: study protocol for a randomized controlled trial

**DOI:** 10.1186/1745-6215-13-175

**Published:** 2012-09-24

**Keywords:** Patient-centeredness, Quality of life, Distress, Multifaceted approach, Determinants, Protocol

## Abstract

**Background:**

Beside traditional outcomes of safety and (cost-)effectiveness, the Institute of Medicine states patient-centeredness as an independent outcome indicator to evaluate the quality of healthcare. Providing patient-centered care is important because patients want to be heard for their ideas and concerns. Healthcare areas associated with high emotions and intensive treatment periods could especially benefit from patient-centered care. How care can become optimally improved in patient-centeredness is unknown. Therefore, we will conduct a study in the context of Dutch fertility care to determine the effects of a multifaceted approach on patient-centeredness, patients’ quality of life (QoL) and levels of distress. Our aims are to investigate the effectiveness of a multifaceted approach and to identify determinants of a change in the level of patient-centeredness, patients’ QoL and distress levels. This paper presents the study protocol.

**Methods/Design:**

In a cluster-randomized trial in 32 Dutch fertility clinics the effects of a multifaceted approach will be determined on the level of patient-centeredness (Patient-centredness Questionnaire – Infertility), patients’ QoL (FertiQoL) and levels of distress (SCREENIVF). The multifaceted approach includes audit and feedback, educational outreach visits and patient-mediated interventions. Potential determinants of a change in patient-centeredness, patients’ QoL and levels of distress will be collected by an addendum to the patients’ questionnaire and a professionals’ questionnaire. The latter includes the Organizational Culture Assessment Instrument about the clinic’s culture as a possible determinant of an increase in patient-centered care.

**Discussion:**

The study is expected to yield important new evidence about the effects of a multifaceted approach on levels of patient-centeredness, patients’ QoL and distress in fertility care. Furthermore, determinants associated with a change in these outcome measures will be studied. With knowledge of these results, patient-centered care and thus the quality of healthcare can be improved. Moreover, the results of this study could be useful for similar initiatives to improve the quality of care delivery. The results of this project are expected at the end of 2013.

**Trial registration:**

Clinicialtrials.gov NCT01481064

## Background

Would it not be great if every hospital worldwide provides consistent, high-quality medical care to all patients? Unfortunately, this is still not daily reality, which underlines the importance of research projects on the improvement of quality of care
[1]. The Institute of Medicine structured the concept of ‘quality of care’ in 2001 by defining six aims around the core need for high-quality healthcare; ‘safety’, ‘effectiveness’, ‘timeliness’, ‘efficiency’, ‘equity’, and ‘patient-centeredness’
[1]. Subsequently, quality measures were developed mainly focusing on safety and effectiveness, while patient-centeredness was often neglected
[1-3]. Patient-centeredness is defined as ‘care that is respectful of and responsive to individual patient preferences and needs and that is guided by patient values’
[1]. Providing patient-centered care is important, because it can build caring relationships between patients and healthcare providers
[4,5], improve health outcomes
[4,6,7], reduce costs
[4,6,8] and increase levels of patients’ quality of life (QoL)
[9].

Healthcare areas associated with high emotions and intensive treatment periods (for example, oncology or rheumatic care) could especially benefit from more patient-centered care. Fertility care is also one of these areas. In developed countries, infertility affects one in six couples who have tried to achieve pregnancy
[10,11]. About 55% of them seek medical help for their problem and start with a longlasting period of fertility workup and/or treatment
[12]. This period is a physical and psychological burden for the couples
[13]. For example, a woman undergoing in *vitro* fertilization (IVF) treatment has to inject herself for several weeks to stimulate the production of oocytes, visit the clinic multiple times for ultrasound check-up and has to undergo transvaginal retrieval of oocytes. After fertilization of the oocytes in the laboratory with sperm, the resulting embryo is transferred to the uterus. Subsequently, the couple has to wait 2 weeks to find out whether pregnancy has occurred. If not, the couple can start a new IVF cycle. Eventually, this treatment period can take several months to even years, which underlines the impact of infertility and its treatment on patient’s QoL. This may be seen in terms of impairments in psychosocial well-being, sexual satisfaction and marital relationship
[13-16]. Moreover, because of the high physical and emotional burden, about 23% of couples end treatment prematurely
[17]. Given these high percentage of patients deciding to terminate treatment early, frequently as a result of high psychological and psychical impact, every clinic should optimize its care towards more patient-centered care
[13,14].

In Dutch fertility care, van Empel and colleagues showed that several parts of patient-centeredness could be improved
[18]. How such improvement initiatives can be undertaken most successfully is still unknown. Moreover, there are potential barriers impeding improvement initiatives. For instance, professionals in fertility care underestimate the importance of patient-centeredness and have difficulties in estimating their performance correctly
[19]. Another barrier may be the organizational culture of a hospital. For instance, patients visiting hospitals that support teamwork are more satisfied with their care than patients visiting hospitals with other culture types (for example, hierarchical culture)
[20-23]. Moreover, providing patient-centered care is often thought to be expensive and time consuming
[24,25].

Obviously, steps need to be taken to achieve a behavioral change in professionals towards providing more patient-centered care. Because no magic bullets exist for changing healthcare providers’ behavior
[26], multiple interventions based on known barriers could accomplish this behavioral change and improve patient-centered care.

We designed a study to evaluate the effects of a quality improvement strategy consisting of three different elements; that is, a multifaceted approach. We hypothesize that providing clinicians with this multifaceted approach will improve the level of patient-centeredness and thus healthcare quality. If so, this is essential in improving patients’ QoL, reducing levels of distress and percentages of patients discontinuing treatment, and eventually reducing healthcare costs.

The main aim of this study is therefore to determine the effects of a multifaceted approach on patient-centeredness, patients’ QoL and levels of distress by: investigating the *effectiveness* of a multifaceted approach for care improvement on patient-centeredness, patients’ QoL and levels of distress; identifying *determinants*, at both patient and clinic levels, of an increase in the level of patient-centeredness, an increase in patients’ QoL and a decrease in distress levels; and performing a *process evaluation* to study the feasibility of the multifaceted approach and gain insight into factors that affected the impact of the intervention.

## Methods/Design

### Setting

In the Netherlands, secondary and tertiary fertility care is provided by three different types of clinics based on the kind of treatment they offer. Initial fertility assessment, ovulation induction and intra-uterine insemination are carried out in all Dutch clinics. The intermediate Dutch clinics can also start up and monitor the IVF and intra-cytoplasmic sperm injection treatments. However, oocyte retrieval and embryo transfer has to occur in one of the 13 licensed clinics (eight university hospitals, four general hospitals, and one private clinic). Almost all Dutch fertility clinics are national health service funded. Every Dutch citizen has a basic insurance coverage, which covers treatment and medication costs for ovulation induction, intra-uterine insemination, and three cycles of IVF/intra-cytoplasmic sperm injection.

### Study population

The study will be performed in a representative Dutch infertile patient group, under treatment in one of 32 Dutch clinics. All couples that participate in this study underwent at least one cycle of medically assisted reproduction (for example, ovulation induction, intra-uterine insemination, IVF, and intra-cytoplasmic sperm injection). Both women and their partners will be invited to participate in this study individually. However, because it is still unknown whether women and partner experiences with patient-centered fertility care are associated, only the women’s data will be used to answer our main research questions. Partners’ data will be used to analyze whether gender is a determinant of patient-centered fertility care. Those couples who are pregnant while completing the questionnaire set will be excluded from all analyses, because most questions about patient-centeredness, patients’ QoL and levels of distress are confounded in this patient group
[18,27,28].

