### Study design

In a cluster-randomized trial, the effects of a multifaceted approach on the level of patient-centered fertility care, patients’ QoL and the level of distress will be identified. To include a representative patient group for baseline measurement, clinics will be asked to extract the address files of all patients who underwent medically assisted reproduction in their clinics during the past 3 months (2011) from their diagnosis treatment combination coding system. Per clinic, 25 to 75 patients will be randomly selected depending on the clinic’s size. Participation is voluntary and anonymous. The couples will receive a letter with an invitation to participate. If they are willing, they complete an online questionnaire set, accessible by a personal code. Two weeks after the initial mailing, all patients will receive a reminder. Another 3 weeks later, nonresponders will receive a reminder with their personal codes and the additional option to complete a paper version of the questionnaire
[29].

Following baseline measurement, all 32 participating clinics will be randomly assigned to usual care (16 clinics) or to the multifaceted approach (16 clinics) with stratification for clinic size (large/medium/small) and IVF facilities (full licensed/intermediate/no IVF facilities).

After 1 year of intervention exposure, all clinics again extract the address files of all patients who underwent medically assisted reproduction in the last 3 months for the after measurement. The same questionnaire set will be used, which again have to be completed by both the women and the partners separately. Figure
1 illustrates the study design schematically.

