### Sample size calculation

To account for a representative number of patients per clinic (that is, 25 to 75 patients per clinic) at least 1,600 couples will be included. The sample size calculation, which was based on the results of the previous Patient-centredness Questionnaire validation study
[18], confirmed that this number of patients is sufficient for a proper analysis. To detect a mean difference score of 0.25 between usual care and the multifaceted approach on patient-centeredness (α = 0.05, two-sided testing, β = 0.8) at least 93 couples are required. Taking into account clustering of couples (30 couples/clinic) and a mean intracluster correlation coefficient of 0.13
[18], 1,023 couples have to be involved. With an expected response rate of 70%
[18], at least 1,462 couples have to be invited at both baseline and after measurement.

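### The minimum of 1,462 invitations allows for non-response only, so it does not deliver the stated 1,023 couples once pregnant responders are excluded

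*Protocol article*

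**What the plan says.** All statements are in the Methods/Design part of the protocol article.

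- **Study population.** "Those couples who are pregnant while completing the questionnaire set will be excluded from all analyses". The stated reason is that most of the questions are confounded in this group. No expected share is given.
- **Study design.** For each wave, clinics "extract the address files of all patients who underwent medically assisted reproduction in their clinics during the past 3 months", and 25 to 75 patients per clinic are drawn at random from those files. No pregnancy check before mailing is described. A general reminder goes out at two weeks. "Another 3 weeks later, nonresponders will receive a reminder" and the option of a paper form.
- **Sample size calculation.** "To detect a mean difference score of 0.25 between usual care and the multifaceted approach on patient-centeredness" (with "α = 0.05, two-sided testing, β = 0.8", where the 0.8 must be the power), "at least 93 couples are required". After clustering (30 couples per clinic, intracluster correlation 0.13) the requirement is 1,023 couples. "With an expected response rate of 70" per cent, "at least 1,462 couples have to be invited at both baseline and after measurement".
- The same section opens with a plan for at least 1,600 couples and says that the calculation confirms this number is enough. It does not say whether the 1,600 are invited or responding.

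**The concern.** Anyone treated in the preceding three months is in the sampling frame, including women whose treatment succeeded. They are invited, may reply, and then count towards the 70%. Only at completion of the questionnaire are they removed from the analysis. The required number in a power calculation has to be the number analysed, but the invitation target is worked back to the number replying. The two sections therefore describe different populations, and the target falls short of its own requirement by the pregnancy share among responders, even if the response rate is met exactly.

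What is at stake is the accuracy of a planning figure that governs two mailings, one of which was still to come when the article was submitted.

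**Working it through.** **Inputs.** From Sample size calculation: 1,023 couples required, 70% response, 1,462 invitations per wave, at least 1,600 couples planned, intracluster correlation 0.13, difference 0.25, unclustered number 93. From Study design: 32 clinics, 16 per arm. Assumed, because the article gives no figure: *p*, the share of responding couples who are pregnant.

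**1. Reproduce the stated figure.** 1,023/0.70 = 1,461.4, rounded up to 1,462. The match is exact, so non-response is the only allowance. In reverse, 1,462 × 0.70 = 1,023.4, and the share that could be lost without falling below 1,023 is 1 − 1,023/1,023.4 = 0.04%.

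**2. Add the pregnancy exclusion.** Analysed = invitations × 0.70 × (1 − *p*). Invitations needed = 1,023/[0.70 × (1 − *p*)], rounded up.

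| Assumed *p* | Analysed from 1,462 | Analysed from 1,600, if invitations | Invitations needed for 1,023 |
|---|---|---|---|
| 2% | 1,003 | 1,098 | 1,492 |
| 5% | 972 | 1,064 | 1,539 |
| 10% | 921 | 1,008 | 1,624 |
| 20% | 819 | 896 | 1,827 |

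**3. What the 1,600 covers.** Read as invitations, 1,600 × 0.70 = 1,120 replies, and 1 − 1,023/1,120 = 8.7%. Read as responders, 1 − 1,023/1,600 = 36%. The first reading fits the mailing plan, since the midpoint of 25 to 75 is 50 and 50 × 32 = 1,600, but the text does not settle it.

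**4. Effect on power.** The article gives no standard deviation, so it is backed out from the 93. If 93 is per arm (the stricter reading), SD = 0.25 × √(93/2)/(1.960 + 0.842) = 0.61. With 32 clinics fixed, exclusions make clusters smaller and so lower the design effect, which offsets most of the loss. At *p* = 10%:

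- couples per clinic = 921/32 = 28.8
- design effect = 1 + 27.8 × 0.13 = 4.61
- effective number per arm = 921/(2 × 4.61) = 99.9
- standardised difference = 0.25/(0.6085 × √(2/99.9)) = 2.90
- power = Φ(2.90 − 1.96) = 83%

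The same steps with 1,462 invited give 83% at *p* = 0, 82% at 20% and 81% at 30%. With a *t*-test on 30 degrees of freedom (32 clinics less 2), power is about 81% at *p* = 0, 80% at 10% and 79% at 20%. If 93 is the total for both arms, the implied SD is 0.43 and power is higher throughout.

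**The case against.** **The plan is 1,600 and 1,462 is only a floor.** This largely stands as a limit on the size of the problem. Read as invitations, 1,600 leaves 97 replies above 1,023; read as responders, it leaves far more. It does not repair the section, because the article never says which reading applies, never links the 1,600 to the pregnancy exclusion, and still gives 1,462 as a sufficient minimum for both waves.

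**The 70% may already be net of pregnancies.** It is taken from the earlier validation study of the questionnaire, which is also among the sources cited for the exclusion. If that rate counted only non-pregnant respondents, the gap would close. The article calls it a response rate and nothing more, so this stays an open condition.

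**The benchmark is itself unsound.** The stated inputs give a design effect of 1 + 29 × 0.13 = 4.77, hence 93 × 4.77 = 444, or 186 × 4.77 = 887 if 93 is per arm. Neither is 1,023. That is a separate defect. It means that missing 1,023 should not be equated with missing 80% power, but it does not make 1,462 the right invitation number for the 1,023 that the article says it needs.

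**Stronger readings that a reader might infer.** One is that the trial is underpowered; step 4 of the working does not show that. Another is selection bias at the after measurement, since pregnancy then arises after randomisation and the Background hopes for fewer patients discontinuing treatment. The article gives no sign of a difference between arms, and the after-sample in both arms is a fresh draw of recently treated patients. On assumed inputs (5 percentage points more pregnancies in one arm, pregnant women differing by 0.3 points, 80% retained) the bias is 0.05/0.80 × 0.3 = 0.019, against a target of 0.25. Replies after the later reminder leave more time to conceive, but that applies to both arms alike. Keeping pregnant responders in a sensitivity analysis would bring back scores that the article regards as confounded; that is a matter of preference and could in any case sit in a fuller plan. None of this carries the point.

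**Conclusion.** The point holds as an inconsistency between the Study population and Sample size calculation sections. The minimum of 1,462 invitations yields 1,023 replies, not 1,023 analysed couples. The shortfall from 1,023 is about 51 couples at an assumed pregnancy share of 5%, 102 at 10% and 204 at 20%. With 1,600 invitations there is no shortfall up to a share of 8.7%, and about 15 couples at 10%.

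This rests on three conditions: that the 70% is not already net of pregnancies, that pregnant couples are not screened out before mailing (no such step is described), and that the pregnancy share, which the article does not give, lies in the assumed range. The consequence for power is one or two percentage points. A claim of inadequate power or of biased arms would go beyond what the article supports. The correction is worth making because it is cheap and the figure sets the size of a mailing still to come.

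**What to change.** Amend the Sample size calculation section in three places.

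1. State that 1,462 invitations are expected to yield about 1,023 replies (or 1,600 invitations about 1,120), rather than that number of couples for analysis.
2. Say whether the 1,600 are couples invited or couples responding.
3. Give the expected analysable number per wave as invitations × 0.70 × (1 − *p*), with *p* taken from the baseline survey, which was complete before clinics were randomised. If the 70% is already net of pregnant couples, say so instead; no further allowance is then needed.

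If the observed *p* exceeds 8.7% and 1,600 means invitations, either raise the number mailed at the after measurement (1,624 at 10%, 1,827 at 20%) or accept the smaller analysed number and state it. The pregnancy exclusion and the main analysis do not change.

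The cost is a few sentences and one count from data already collected. The downside is a slightly less favourable analysable number and, if the mailing is enlarged, some extra postage and clinic effort.

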### Ethical approval

The Regional Review Board for Research on Human Subjects (CMO) has received full ethical approval for this project (CMO No. 2011–034). The study is registered at clinicaltrials.gov NCT01481064.

### Study design

In a cluster-randomized trial, the effects of a multifaceted approach on the level of patient-centered fertility care, patients’ QoL and the level of distress will be identified. To include a representative patient group for baseline measurement, clinics will be asked to extract the address files of all patients who underwent medically assisted reproduction in their clinics during the past 3 months (2011) from their diagnosis treatment combination coding system. Per clinic, 25 to 75 patients will be randomly selected depending on the clinic’s size. Participation is voluntary and anonymous. The couples will receive a letter with an invitation to participate. If they are willing, they complete an online questionnaire set, accessible by a personal code. Two weeks after the initial mailing, all patients will receive a reminder. Another 3 weeks later, nonresponders will receive a reminder with their personal codes and the additional option to complete a paper version of the questionnaire
[29].

Following baseline measurement, all 32 participating clinics will be randomly assigned to usual care (16 clinics) or to the multifaceted approach (16 clinics) with stratification for clinic size (large/medium/small) and IVF facilities (full licensed/intermediate/no IVF facilities).

After 1 year of intervention exposure, all clinics again extract the address files of all patients who underwent medically assisted reproduction in the last 3 months for the after measurement. The same questionnaire set will be used, which again have to be completed by both the women and the partners separately. Figure
1 illustrates the study design schematically.

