### Questionnaires

The questionnaire set consists of three different questionnaires and some additional background questions for case-mix adjustment and to identify possible determinants of a change in the levels of patient-centeredness, patients’ QoL and distress levels.

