#### Effectiveness of the multifaceted approach

To analyze the effectiveness of the multifaceted approach on patient-centeredness, patients’ QoL and levels of distress, the difference in baseline and after-measurement scores will be analyzed with adjustment for clustering of patients within clinics. Multilevel linear regression analyses will therefore be performed in which the intervention (multifaceted approach vs. usual care) will act as the independent variable. The Patient-centredness Questionnaire – Infertility total and subscale scores, the FertiQoL total scores and the SCREENIVF scores will be used as dependent variables. Differences at baseline will be corrected for by taking baseline scores as a covariate in the final multilevel models.

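### The effectiveness model as stated omits the two factors used to stratify the randomisation; if they predict outcome beyond the baseline score, the test is conservative and a little precision is lost

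*Protocol article*

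**What the plan says.** Under Study design, the 32 clinics are allocated 16 to 16 after the baseline measurement, "with stratification for clinic size (large/medium/small) and IVF facilities (full licensed/intermediate/no IVF facilities". That is two factors of three levels each.

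The section on effectiveness describes multilevel linear regression that allows for patients being clustered in clinics, "in which the intervention (multifaceted approach vs. usual care) will act as the independent variable". It adds the baseline score as a covariate in the final models and names no other covariate.

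The Questionnaires section says that the set includes "some additional background questions for case-mix adjustment". The effectiveness section does not mention case-mix again. Patient and clinic characteristics reappear by name only in the analysis of determinants.

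**The concern.** Stratified allocation makes the arms alike on clinic size and IVF facilities, so differences between strata contribute little to the true sampling variation of the treatment contrast. A model that does not know about the strata still counts those differences as error. If the factors are prognostic, the reported standard error is then larger than it need be, the confidence interval too wide and the test conservative. With 32 clinics and an intracluster correlation of 0.13, most of the variance of a clinic mean lies between clinics, which is where the strata act. What is at stake is precision that the design has already paid for, not false-positive risk.

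Case-mix is a lesser and different matter. The after-measurement draws a new three-month patient file once clinics know their allocation, so the respondents may differ between arms in ways that a baseline score from other women does not capture.

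**Working it through.** **Inputs from the protocol article.** Sample size calculation: "To detect a mean difference score of 0.25 between usual care and the multifaceted approach on patient-centeredness"; "α = 0.05, two-sided testing, β = 0.8" (the 0.8 is read as power); "at least 93 couples are required"; "Taking into account clustering of couples (30 couples/clinic) and a mean intracluster correlation coefficient of 0.13". Study design: 32 clinics, 16 per arm, two three-level factors.

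**Assumptions, because the article gives no figure.**
- The share *s* of between-clinic variance explained by the strata: 0, 20, 50 or 80%.
- The correlation *ρ* between a clinic's baseline and after level, apart from the strata: 0.5 or 0.8.
- Equal clinics of 30 respondents.
- The baseline score enters as the clinic mean.

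**The plan's own figures.** The article gives no figure for the effect of the strata. Its sample size is only a source of inputs here. The design effect is 1 + 29 × 0.13 = 4.77, which gives 93 × 4.77 = 444, or 186 × 4.77 = 888 if 93 is per arm. Neither is the stated 1,023. The last step does reproduce: 1,023/0.70 = 1,462. That gap is a separate matter and does not enter below.

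**Standard deviation.** None is stated. Solving σ = δ√{n/[2(1.96 + 0.842)²]} gives 0.25 × √(93/15.70) = 0.61 if 93 is per arm, and 0.25 × √(46.5/15.70) = 0.43 if it is the total.

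**Hand check of the standard-error ratio.** In units of the total variance, a clinic mean has variance 0.13 + 0.87/30 = 0.159.
- Without strata in the model, the baseline–after covariance is 0.13[*s* + (1 − *s*)*ρ*] and the residual variance is 0.159 − covariance²/0.159.
- With strata in the model, V = 0.13(1 − *s*) + 0.029, the covariance is 0.13(1 − *s*)*ρ* and the residual variance is V − covariance²/V.

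For *s* = 0.2, *ρ* = 0.5: without, 0.159 − 0.078²/0.159 = 0.1207; with, 0.133 − 0.052²/0.133 = 0.1127. Ratio of standard errors √(0.1207/0.1127) = 1.035.

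For *s* = 0.5, *ρ* = 0.5: without, 0.159 − 0.0975²/0.159 = 0.0992; with, 0.094 − 0.0325²/0.094 = 0.0828. Ratio √(0.0992/0.0828) = 1.095.

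**Simulation.** Stratified 16:16 allocation and regression of clinic means (equivalent to a random-intercept model when clinics are equal in size), with t tests on the residual degrees of freedom: 32 − 3 = 29 without the factors and 32 − 7 = 25 with them. There were 1,500 runs per scenario, SD 0.609 and difference 0.25. Both models contain the clinic baseline mean.

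| *s* | *ρ* | Mean SE without / with factors | SE excess | Power without / with |
|---|---|---|---|---|
| 0% | 0.5 | 0.0794 / 0.0794 | 0% | 84.5% / 84.1% |
| 0% | 0.8 | 0.0658 / 0.0659 | 0% | 94.9% / 94.8% |
| 20% | 0.5 | 0.0751 / 0.0725 | 3.6% | 89.3% / 90.0% |
| 20% | 0.8 | 0.0629 / 0.0619 | 1.6% | 97.1% / 97.3% |
| 50% | 0.5 | 0.0688 / 0.0632 | 9% | 93.9% / 96.2% |
| 50% | 0.8 | 0.0581 / 0.0554 | 5% | 98.3% / 98.9% |
| 80% | 0.5 | 0.0578 / 0.0494 | 17% | 98.5% / 99.8% |
| 80% | 0.8 | 0.0531 / 0.0471 | 13% | 99.5% / 99.8% |

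The simulated type I error of the model without the factors lay between 3.9% and 5.5%. The Monte Carlo error is about √(0.05 × 0.95/1,500) = 0.6 points, so there is no sign of inflation. With SD 0.43, power is about 99% or more throughout.

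**If no baseline covariate is usable.** At *s* = 50%, the mean standard error without the factors is 0.086 against a true value of about 0.065. Type I error is about 1%, and power is about 85% against 95% with the factors.

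**The case against.** The strongest objection is that silence is not exclusion. The effectiveness section is a short summary in a journal article, and a full analysis plan, not shown, may list the stratification factors. That stands as a limit: the article does not prove that they will be left out. It does describe the final models and name a covariate for them, so adding the factors used in the randomisation is a definite improvement to the model as stated and not a request for detail.

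The second objection concerns size. A reader might infer that standard errors are certainly too large and power materially lost. Without a baseline covariate, at 32 respondents per clinic (1,023/32), the clinic-mean variance is 0.13 + 0.87/32 = 0.157, of which 0.13/0.157 = 83% lies between clinics. Strata explaining 20–30% of that part would then overstate the standard error by about 9–15%, lower type I error to about 3.2–2.4%, and leave about 74–71% power where the adjusted test has 80%. The arithmetic is right, but it describes a model that the article does not plan, and the 20–30% is an assumption. The section on the intervention reports large variation between clinics without attributing it to size or IVF facilities. With the planned baseline covariate as a clinic mean, the loss at 20% is under 1 point of power.

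The reply has some force too. The article does not say that the covariate is a clinic mean. Because the after-measurement uses a fresh patient file, many women may have no baseline score of their own.

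On case-mix, a reader might infer that adjustment has been dropped and the estimate is biased. The documents do not support that: the intention to adjust is stated, and the effectiveness section merely does not repeat it.

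**Conclusion.** The point holds in a conditional and modest form. The design stratifies on two factors that the stated effectiveness model does not name. If they predict outcome beyond the baseline score, the standard error is somewhat too large and the test conservative.

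With a clinic-mean baseline covariate, the excess over the model with the factors is about 0–4% when the strata explain up to 20% of between-clinic variance and 5–9% at 50%. The corresponding power loss is about 0–2 points. It is zero if the factors are not prognostic, and larger if no usable baseline covariate is available. These sizes rest on a back-solved SD, assumed correlations of 0.5 to 0.8 and equal clinics of 30. The validity of a positive result is not threatened by omitting the strata. The case-mix part is a matter of reconciling two sections; no size can be put on it from the article.

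**What to change.** In the effectiveness section, add clinic size (three levels) and IVF facilities (three levels) as fixed main effects in every multilevel effectiveness model, and keep the model without them as a sensitivity analysis. This uses 2 + 2 = 4 of about 30 clinic-level degrees of freedom and needs no new data, since both factors are known at randomisation. If the factors turn out not to be prognostic, the simulated cost is 0.1–0.4 points of power.

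State in the same place whether the baseline covariate is the clinic mean, because the size of the gain depends on it.

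Secondarily, reconcile Questionnaires with the effectiveness section: name in advance the case-mix variables intended for adjustment, restricted to those that the intervention cannot change (age, education or cause of infertility, for example, from the listed patient characteristics), and include them in the effectiveness model.
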